#### 6.4. Missing data

Missing baseline and outcome data will be summarized by study arm. As outlined above, the primary analyses will be the intent-to-treat population. In the case of missing data or drop-outs, we may adjust for further baseline variables which are associated with missing outcome data or we consider multiple imputation. Both, baseline patient characteristics and outcome variables will be considered for multiple imputations. Variables with more than 50% missing values will not be used for the imputation model. Categorical variables with a frequency of 5% or less in one category will also be omitted. Continuous variables will be imputed using linear regression and binary variables using logistic regression. We will construct and analyze 20 imputed data sets and combine results using Rubin's rules. Diagnostic checks, including model convergence and comparing observed versus imputed distributions, will be performed to ensure the quality of imputations.

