### 6.3. Analysis methods

#### 6.3.1 Primary analysis

Analysis of the primary endpoint will follow the intention-to-treat (ITT) principle. It will be based on the FAS with missing data of the primary outcome imputed as described in the section “Missing data” (section 6.4). Patient data will be analysed according to their intervention allocation, irrespective of actual treatment received.

The primary outcome, surgical intervention time, will be assessed using a linear regression model. The estimates will be reported with 95% confidence intervals (CI). Explanatory variables will be BMI, underlying diagnosis, experience surgeon and the use of an old burr hole.

In case the outcome variable is not normally distributed, data will be transformed or a different model, depending on the distribution of the data, chosen.

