##### 6.3.1.2. Analysis of secondary outcomes

All analysis of the secondary endpoints will follow the intention-to-treat (ITT) principle. It will be based on the FAS with missing data of the primary outcome imputed as described in the section “Missing data” (section 6.4).

The continuous secondary endpoints (outcomes operation time, anaesthesia time, volumetry of side ventricles, and Evan’s Index) will be assessed using linear regression models, the binary endpoints (optimal catheter placement, complications, mortality and revision surgery) will be assessed using logistic regression, and the number of puncture attempts will be assessed using a poisson regression model.

All estimates will be reported with 95% CI. IF numbers allow explanatory variables will be BMI, underlying diagnosis, experience surgeon and the use of an old burr hole.

In case the outcome variable is not normally distributed or model assumptions are violated, data will be transformed or a different model, depending on the distribution of the data, chosen.

Deviation from the original statistical plan:

If substantial deviations of the analysis as outlined in these sections are needed for whatever reason, the protocol will be amended. All deviations of the analysis from the protocol or from the detailed analysis plan will be listed and justified in a separate section of the final statistical report.

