## 9.3 Procedures at each visit

### 9.3.1 Visit 1: Screening and admission

Randomisation, demographics (age, gender), height, weight, body mass index (BMI), neurologic examination (GCS, modified Rankin Scale (mRS), Glasgow Outcome Scale (GOS), neurological symptoms (headaches, vomitus, coma, gait disturbances, dementia, urinary incontinence, motor deficit, sensory deficit, aphasia, delir, others), medical history (underlying disease causing hydrocephalus (NPH, SAH, IVH, other type of bleeding, trauma, tumor, congenital, other), prior EVD, prior VPS, or prior head operations including details), cCT scan (US group not older than 90 days, stereotactic navigation group not older than 5 days, measurements: Evans' index, volumetry of side ventricles). Randomisation and cCT scan (indications see above) is the only measurements done for the study, all the other measurements are generally assessed for all patients receiving this operation.

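### The 5% rule in SAP 6.4 can drop underlying diagnosis from the imputation model while the primary analysis model keeps it

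*Combined protocol and SAP*

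**What the plan says.** SAP 6.4 sets two exclusions for the imputation model. The first concerns missingness: "Variables with more than 50% missing values will not be used for the imputation model". The second follows directly and concerns sparseness: "Categorical variables with a frequency of 5% or less in one category will also be omitted". The section does not exempt covariates of the analysis model and does not provide for merging small categories. On scope it states "Both, baseline patient characteristics and outcome variables will be considered for multiple imputations", and on method "Continuous variables will be imputed using linear regression and binary variables using logistic regression". No method is named for a variable with more than two categories. Multiple imputation itself is optional: the SAP may adjust for further baseline variables "or we consider multiple imputation".

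SAP 6.3.1 says missing primary outcomes are imputed under 6.4 and fixes the covariates of the model: "Explanatory variables will be BMI, underlying diagnosis, experience surgeon and the use of an old burr hole". SAP 6.3.1.2 uses the same covariates for the secondary outcomes, but only if numbers allow, and opens with "All analysis of the secondary endpoints will follow the intention-to-treat (ITT) principle". Protocol 9.3.1 lists the categories of diagnosis: "underlying disease causing hydrocephalus (NPH, SAH, IVH, other type of bleeding, trauma, tumor, congenital, other"), which makes eight.

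**The concern.** An imputation model should contain at least the variables of the analysis model. If a covariate is left out, values are imputed as though the outcome did not depend on it given the other predictors, and the analysis model then adjusts for it. The SAP rule produces this mismatch for diagnosis as soon as one of its eight categories is sparse, because it discards the variable and not just the sparse category.

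The treatment estimate is at risk if three things hold together: diagnosis is related to the outcome, it is related to who is lost, and the loss within diagnosis differs between the arms. A missing diagnosis value would also have no route to imputation. The same could happen to any other categorical covariate of the model with a sparse category. Diagnosis is the most exposed because it has so many.

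**Working it through.** **Inputs from the documents.** Threshold 5% (SAP 6.4). Eight diagnosis categories (protocol 9.3.1). Total sample 130 (SAP 2.3) or 136 (protocol 11.2). Diagnosis frequencies: none given.

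**Denominator.** The SAP's 58 per group reproduces from a two-sided 5% test with 80% power, a difference of 15 min and an SD of 28.65 min. Inflating for 1% drop-out and 5% non-adherence gives 58 / (0.99 × 0.95²) = 64.9, so 65 per group and 130 in total. The protocol adds 6 to reach 136.

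**Cut-off as a count.** I count frequency over both arms together. 0.05 × 130 = 6.5 and 0.05 × 136 = 6.8. Under either total, 6 or fewer patients in a category triggers omission, and diagnosis survives only if all eight categories hold at least 7.

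**When omission is certain.** Seven categories at the minimum of 7 use 49 patients. If the largest category exceeds 136 − 49 = 87 patients (64%), or 130 − 49 = 81 (62%), the other seven cannot all reach 7.

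**One category with true share p.** P(X ≤ 6), X ~ Binomial(N, p):

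| p | N = 130 | N = 136 |
|---|---|---|
| 3% | 0.90 | 0.88 |
| 5% | 0.52 | 0.48 |
| 8% | 0.10 | 0.08 |
| 10% | 0.02 | 0.01 |

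**All eight categories.** P(smallest count ≤ 6) under a multinomial, 200,000 draws per row. Every mix is an assumption.

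| Assumed mix (%) | N = 130 | N = 136 |
|---|---|---|
| 12.5 each | 0.02 | 0.01 |
| 30, seven at 10 | 0.14 | 0.10 |
| 35, 15, 10, five at 8 | 0.43 | 0.35 |
| 40, 20, 10, 8, 7, 6, 5, 4 | 0.95 | 0.93 |
| 50, 20, 10, 5, 5, 5, 3, 2 | >0.999 | >0.999 |

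Omission is therefore likely once one category has a true share of about 4–5% or less and another is not much larger, and unlikely if the mix is near even.

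**Effect on the estimate.** A simulation of 1,500 trials, with 20 imputations combined by Rubin's rules, assumed about 15% missing outcomes, diagnosis shifts of up to 0.8 SD and a true effect of 0.5 SD. None of these values comes from the documents.

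- With 40% missing among bleeding diagnoses in one arm and 10% elsewhere, the bias was −0.049 SD with diagnosis omitted and +0.007 SD with it included. As a share of the effect, 0.049 / 0.5 is about 10%.
- With loss not differing by arm, there was no bias and a slightly larger standard error.

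**The case against.** The strongest case against is that the rule acts where little is missing. Only the primary model contains diagnosis unconditionally, and surgical time is recorded for every operation (protocol 9.2.1) with 1% drop-out anticipated. In the secondary models diagnosis enters only if numbers allow; if it is left out there, the mismatch disappears. Multiple imputation is optional in SAP 6.4, and protocol 11.5 mentions it only as a possible sensitivity analysis. SAP 6.3.1.2 literally speaks of imputing the primary outcome. SAP 4.4 limits the full analysis set to patients with completed follow-up, so on a literal reading those lost before the 6-month CT are never imputed (protocol 11.4.1 includes everyone randomised). Other baseline data and the early postoperative CT could serve as predictors and reduce the bias. Leaving out sparse variables is also a recognisable guard against unstable fits at this sample size.

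All of this stands, and it limits the size of the point. It does not justify the rule, because merging categories gives the same protection without losing the covariate.

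A reader might go further in two ways that the documents do not support. One is that diagnosis will probably be dropped: with no frequencies given, any probability depends on the assumed mix. The other is that rare safety outcomes are lost. Death and coma, expected in under 1% (protocol 5.4), would almost certainly leave the imputation model: even at a true rate of 1%, or 1.36 events in 136, the chance exceeds 0.999. They are still analysed and reported as observed under SAP 6.3.1.2 and 6.5, which is a reasonable way to treat such rare events. No rate is stated for the other safety events.

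**Conclusion.** The point holds as a cheap improvement. SAP 6.4 states a rule that, with one diagnosis category of 6 or fewer patients, makes the imputation model smaller than the analysis model in SAP 6.3.1. The chance of this cannot be fixed from the documents and runs from about 1% to over 99% across the assumed mixes. The consequence depends on multiple imputation being used and falls mainly on follow-up and 6-month CT outcomes, if these are imputed. The bias of about 0.05 SD belongs to one constructed scenario of differential loss and vanishes when loss does not differ by arm. The primary result is not in question.

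**What to change.** Replace the 5% sentence in SAP 6.4 before database lock with a rule of this kind: the imputation model always includes treatment arm, the outcome being analysed and every covariate of the corresponding analysis model; sparse categories are merged by a rule fixed before database lock, and the variable is not omitted. The merged variable should be used in both models so that they match. If a variable with more than two categories itself needs imputing, use a multinomial model.

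The cost is one or two sentences and no new data. The downside is some loss of detail where categories are merged.

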#### 6.5. Evaluation of safety parameters

Evaluation of safety parameters will be based on the safety population (FAS, section 4.4). They will be listed according to the treatment the patient actually received with the time points of onset. If many adverse events should be observed, we will compare frequency between treatment groups.

Safety endpoints are the following events: positioning of the catheter, number of ventricle puncture attempts, VPS dysfunction, revision rate, perioperative complications (bleeding, infection), complications due to head clamp, death, and coma.

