### 7. Changes from the protocol

None.

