### **4.3 Secondary Objectives**

Further we are interested in special aspects of safety and feasibility of the navigation methods in direct comparison to each other, such as positioning of the catheter (optimal/not optimal, grade I to IV, safety), rate of VPS dysfunction and revision surgery (safety), number of ventricular puncture attempts that have been made (safety and feasibility), operation and anaesthesia times (feasibility), and any complications and morbidity (safety), as well as death (safety).

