#### **11.4.5 Safety analysis**

Safety will be assessed via a rigorous and detailed examination of adverse events between the treatment group and the control group. Safety endpoints will be assessed using the FAS.

Safety endpoints are the following events: positioning of the catheter, number of ventricle puncture attempts, VPS dysfunction, revision rate, perioperative complications (bleeding, infection), complications due to head clamp, death, and coma.

Binary safety endpoints will be compared as number of events between the two groups (US and stereotactic navigation) using a logistic regression. To compare the number of ventricle puncture attempts per patient between the treatment and control arm we will use a Poisson regression model.

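### SAP 6.5 compares adverse events between groups only if 'many' occur, against the unconditional comparison in protocol 11.4.5, so no effect estimate is assured for VPS dysfunction, coma or adverse events overall

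*Combined protocol and SAP*

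**What the plan says.** SAP 6.5 bases the safety evaluation on the FAS and first provides for a listing: "They will be listed according to the treatment the patient actually received with the time points of onset". The only provision for a between-group comparison in that section is "If many adverse events should be observed, we will compare frequency between treatment groups". The section then names eight endpoints: "Safety endpoints are the following events: positioning of the catheter, number of ventricle puncture attempts, VPS dysfunction, revision rate, perioperative complications (bleeding, infection"), followed by head-clamp complications, death and coma.

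Protocol 11.4.5 names the same endpoints and attaches no condition. It promises this: "Safety will be assessed via a rigorous and detailed examination of adverse events between the treatment group and the control group". For the endpoints it adds "Binary safety endpoints will be compared as number of events between the two groups (US and stereotactic navigation) using a logistic regression" and "To compare the number of ventricle puncture attempts per patient between the treatment and control arm we will use a Poisson regression model".

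Protocol 4.3 includes among the secondary objectives the "rate of VPS dysfunction and revision surgery (safety"). The SAP section headed "Changes from the protocol" contains only the entry None.

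**The concern.** A comparison that is triggered by the number of events observed, with no number stated, is decided after the data are known. Nobody can tell beforehand whether it will be made. The surgeons in this trial are not blinded, and feasibility and safety are its stated main objective (SAP 1.2, protocol synopsis). An analysis rule that leaves room for discretion on safety therefore weakens the report whichever way the discretion is used.

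The endpoint most exposed is VPS dysfunction. The protocol's own rationale (3.1) is that the position of the ventricular catheter influences shunt malfunction. Dysfunction is assessed up to the 6-month visit, yet it is missing from the SAP's list of secondary outcomes and from its secondary models. A moderate imbalance could appear as two counts in a table with no estimate of the difference and no interval.

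**Working it through.** The plan gives no figure on this point to reproduce, so the check is mainly a comparison of texts.

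**Step 1. Which safety endpoints have an unconditional comparison elsewhere in the SAP?** The eight endpoints of SAP 6.5 are set against the models in SAP 6.3.1.2 and the outcome list in SAP 6.1.

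| Safety endpoint | Protocol 11.4.5 | SAP 6.3.1.2 |
|---|---|---|
| Catheter position | compared | logistic, as optimal or not |
| Puncture attempts | Poisson | Poisson |
| Revision | logistic | logistic |
| Bleeding, infection | logistic | logistic, within complications |
| Head-clamp complications | logistic | only within complications (navigation-related) |
| Death | logistic | logistic |
| VPS dysfunction | logistic | none |
| Coma | logistic | none |

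Six of the eight have an unconditional model, one of them only inside a composite. Two have none. The phrase in SAP 6.3.1.2 about numbers allowing restricts the covariates, not the comparison.

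**Step 2. Do other SAP sections fill the gap?** SAP 4.1 requires descriptive tables by group, with absolute and relative frequencies, so counts by arm will be shown. It promises no estimate of the difference. SAP 4.2 attaches an effect measure and a 95% CI to tests; where no test is made, none is assured. SAP 2.4 says in general terms that all endpoints are analysed for superiority, but it names no model, and 6.5 is the specific rule for safety.

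**Step 3. How much turns on the undefined word?** Assumptions: a true event rate p common to both arms and N = 136 (protocol) or 130 (SAP). The documents give a rate only for death and coma (under 1%), so the 5% and 10% rows are illustrations. P(at least k events) is the upper tail of Binomial(N, p).

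| p | k | N = 136 | N = 130 |
|---|---|---|---|
| 5% | 5 | 0.82 | 0.78 |
| 5% | 10 | 0.14 | 0.12 |
| 10% | 10 | 0.88 | 0.85 |
| 10% | 15 | 0.39 | 0.32 |

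If 'many' means 5, the comparison would usually be made at a 5% rate. If it means 10, it would usually not be made.

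**Step 4. What size of difference could be left without an estimate?** The counts are again assumed. For each arm take the Wilson limits (l, u) of the proportion p. The Newcombe limits for d = p1 − p2 are

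lower = d − √[(p1 − l1)² + (u2 − p2)²], upper = d + √[(u1 − p1)² + (p2 − l2)²].

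For 10/68 against 3/68:
- p1 = 0.1471, Wilson 0.0819 to 0.2500; p2 = 0.0441, Wilson 0.0151 to 0.1219.
- d = 0.1029; lower = 0.1029 − √(0.0652² + 0.0778²), about 0.001; upper = 0.1029 + √(0.1029² + 0.0290²), about 0.210.
- In percentage points: 10.3 (0.1 to 21.0).

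For 8/68 against 2/68 the same formula gives 8.8 points (−0.3 to 18.8). With the SAP's 65 per arm the two results are 10.8 (0.2 to 21.9) and 9.2 (−0.3 to 19.6).

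**The case against.** The strongest reply is that safety is largely compared anyway. A reader of SAP 6.5 alone might infer that whether safety is compared at all depends on the data. The documents do not support that: six of the eight endpoints have unconditional models, and by-group counts are required for all of them. An imbalance in dysfunction would be visible. This part of the reply stands and limits the point to what has no assured estimate.

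Second, it is not certain that the condition reaches VPS dysfunction. Protocol 9.2.4.1 defines adverse events for this trial as death and complications referable to a navigation method, while 10.3.1 uses the broad definition. The ambiguity is real but does not close the gap. On the broad reading, dysfunction is compared only if events are many. On the narrow reading, no SAP sentence provides for comparing it.

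Third, revision surgery is modelled, and its recorded indications include obstruction, disconnection and dislocation. Dysfunction that leads to revision is therefore largely captured. But the protocol records dysfunction separately, with its own categories, and promises its own comparison.

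Fourth, a comparison for coma would say little. At 1%, the upper end of the stated expectation, 136 × 0.01 gives about 1.4 events. That is correct, and is a reason to expect a wide interval rather than to make the analysis conditional.

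Fifth, the example counts are invented. They are, and Fisher's exact p-values for them are 0.077 and 0.096. They show only what intervals 10 to 13 events can produce; they predict nothing, and the documents set no margin by which to call such differences clinically relevant.

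**Conclusion.** The point holds in a limited form. SAP 6.5 contains a data-dependent rule with an undefined trigger. It conflicts with protocol 11.4.5, and SAP section 7 does not declare it. The consequence is that a between-arm estimate with a confidence interval is not assured for VPS dysfunction, coma, or adverse events overall, and head-clamp complications have no comparison of their own.

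The textual conflict rests on no assumption. The sizes do: the event rates and the counts of 10 and 3 or 8 and 2 are illustrative, because the documents give no dysfunction rate. The primary endpoint and the sample size are not affected. The change is worth making because safety is part of the main objective and the remedy costs almost nothing.

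**What to change.** Delete the conditional sentence in SAP 6.5 and state instead:

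- Every binary safety endpoint in protocol 11.4.5, with VPS dysfunction, coma and head-clamp complications each named, is compared between allocated arms whatever its frequency, using the protocol's logistic regression.
- Each is also reported as number, percentage and risk difference with a Newcombe 95% CI. Where events are too sparse for the logistic model to fit, for example none in one arm, the risk difference stands alone.
- Puncture attempts keep Poisson regression; a risk difference does not suit a count per patient.
- The listing by treatment received remains as a supplementary display.
- The SAP says which definition of adverse event applies to the overall comparison, 9.2.4.1 or 10.3.1.

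Record the added risk differences in SAP section 7, since protocol 11.4.5 does not mention them. The cost is one rewritten sentence and a few table rows, with no change to data collection or sample size. The downside is a few wide, uninformative intervals for rare events such as coma. If the sponsor prefers to keep a condition, the threshold and method must be stated and the departure declared in SAP section 7.

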#### 6.6. Statistical software

The statistical analysis will be performed by Surgical Outcome Research Center using the statistical software R (Version 4.3.2, The R Foundation for Statistical Computing, Vienna, Austria).

### 7. Changes from the protocol

None.

## STUDY SYNOPSIS

|                                       |                                                                                                                                                                                                                                                                                                                                                                                                                                                                                                                                                                                                                                                                                                                                                                                                                                                                                                                                                                                                                                                                                                                                                                                                                                                                                                                                                                                                                                                                                                                                                                                                                                                                                                                                                                                                                                                                                                                                                                                                                                                                                                                                                                                                                                                                                               |
|---------------------------------------|-----------------------------------------------------------------------------------------------------------------------------------------------------------------------------------------------------------------------------------------------------------------------------------------------------------------------------------------------------------------------------------------------------------------------------------------------------------------------------------------------------------------------------------------------------------------------------------------------------------------------------------------------------------------------------------------------------------------------------------------------------------------------------------------------------------------------------------------------------------------------------------------------------------------------------------------------------------------------------------------------------------------------------------------------------------------------------------------------------------------------------------------------------------------------------------------------------------------------------------------------------------------------------------------------------------------------------------------------------------------------------------------------------------------------------------------------------------------------------------------------------------------------------------------------------------------------------------------------------------------------------------------------------------------------------------------------------------------------------------------------------------------------------------------------------------------------------------------------------------------------------------------------------------------------------------------------------------------------------------------------------------------------------------------------------------------------------------------------------------------------------------------------------------------------------------------------------------------------------------------------------------------------------------------------|
